### Randomization

2.7

Random numbers will be generated by PEMS 3.1, and made into random cards. Then the cards will be sealed in opaque envelopes, kept by designated personnel. There is a one-to-one correspondence between the registration of clinic patients and the serial number of the envelope which contains the random number. Based on the number of the envelope each patient gets, these 70 patients will be grouped into the intervention group and the control group at random, and each group will contain 35 samples.

### Blinding

2.8

Since it is unachievable to apply blind method to experimental subjects of the two groups above and the experimenters, result measurers and data statisticians will be blinded.

### Intervention

2.9

At the screening visit, participants will sign the informed consent form. In a baseline questionnaire, information will be obtained age, occupation (physical/non-physical), education level, last menstrual period, previous use of acupuncture and expectation to acupoint catgut embedding therapy. Moreover, Panic Disorder Severity Score (PDSS), Panic-associated Symptoms Score (PASS), Hamilton Anxiety Scale (HAMA), Symptom Checklist 90 (SCL-90) must be completed at the baseline (week 0). The frequency of panic attack will also be recorded. Thereafter, study subjects will be randomized. There is a 3-months study period and a 1-month follow-up period for each group. In the study period, the frequency of panic attack, PDSS, PASS, HAMA Score and SCL-90 Score will be evaluated every 4 weeks. fMRI and 1H-MRS will be tested two times: in week 0 and week 12. A detailed process flow according to the SPIRIT figure can be seen in Table 1.

**Table 1 T1:**
[figure not shown]
Schedule of enrollment, interventions and assessments.

#### Intervention group

2.9.1

Acupoint catgut embedding therapy will be applied to patients in the intervention group fortnightly, a total of 6 times during 3 months. Main acupoints are BL23, SP6 and RN4. If it is a liver-kidney yin deficiency case, BL18 will be added. If it is a kidney yang deficiency case, ST36 and BL20 will be included. In each treatment, RN4 is a required acupoint. The rest acupoints can be used in the alternation of left/right side. The location method is according to *Location of Acupoints* the National Standards of P.R promulgated by the State Bureau of Technology Supervision. The operating method follows the National Standards of P.R (GB/T 21709.10-2008) manipulations of acupuncture and moxibustion—Part 10 Acupoint catgut embedding. Details about the intervention group interventions are described in the Standards for Reporting Interventions in Clinical Trials of Acupuncture (STRICTA) checklist in Table 2.^[14]^

**Table 2 T2:**
[figure not shown]
Details of acupuncture treatment for perimenopausal panic disorder, based on the STRICTA 2010 checklist.

#### Control group

2.9.2

In the 3-months study period, patients in the control group will take Alprazolam tablet (Guangxi Southpearl Pharmaceutical Co., Ltd.) with the size of 0.4 mg orally, 1 tablet a time, 3 times a day.

#### fMR examination procedure

2.9.3

The fMRI (PRISMA 3.0T Magnetic Resonance Imaging Scan; Siemens Company) examination will be performed to collect brain images offering more visualized proof. During the scanning procedure, subjects will be asked to keep quiet and their eyes closed. In the meantime, they need to empty their minds but avoid sleeping. The researcher will check whether the participants are awake during the process. For T1-weighted images (Spin Echo) scan, parameters are TR/TE = 2100 ms/24 ms, field of view = 240 mm × 240 mm, matrix size = 256mm × 256 mm, voxel size = 3 × 3 × 3mm^3^, 18 sections, 5 mm thickness, 1.5 mm slice gap, 20.83 Hz/pixel bandwidth. DTI images (SE EPI), in transaxial plane aligned to the anterior and posterior commissure line, are acquired with the following parameters: matrix size = 128mm × 28 mm, field of view = 240mm × 240 mm, 3.8 mm slice thickness, 28 slices centered on the corpus callosum, b-value = 1000 s/mm^2^. The parameters of T2-weighted images (Gradient-Echo, Echo Planar imaging, GRE-EPI) are TR/TE/FA = 3000ms/60ms/90°, field of view = 240mm × 240 mm, matrix size = 64mm × 64 mm, 18 sections, 5 mm thickness. The data acquisition is carried out 12 seconds after the start of scanning, and the scanning time is 5 minutes and 12 seconds. The blood oxygen level dependent (BOLD) signal imaging sequence is monitored by RTIP.

#### 1H-MRS examination procedure

2.9.4

1H-MRS data are acquired with GE EXCITE Signa 3.0T MR. Structural images for orientation using the following parameters: the axial and coronal plane, TR/TE = 3647 ms/100 ms, 1 mm thickness, no slice gap. 1H-MRS voxels are positioned in the Hypothalamus (1.5 × 1.5 × 1.0 cm). Spectra are acquired using Point Resolved Spectroscopy (TE = 144 ms; TR = 1500 ms; NEX8) and analyzed using SPM8 software provided by the Philips Company. The position of N-acetyl-aspartate (NAA) is determined at 2.0 ppm on the spectral line, and the chemical shifts of other substances are determined with NAA as reference. So Glutamic acid complex (Glx, Glu + Gln) is located at 3.8 ppm, GABA is located at 3.0 ppm, acetylcholine complex (Cho) is located at 3.2 ppm, creatine (Cr) is located at 3.02 ppm. The area under each peak is measured in the calculation. The ratio of NAA, Cho to Cr is calculated with Cr as the internal standard.

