#### fMRI and 1H-MRS

2.10.3

fMRI will focus on the activity of the amygdaloid nucleus and the connection between the fear center and fear network to reflect the changes of the brain's function of perimenopausal PD patients before and after treatment. 1H-MRS will test the Glutamate-GABA level of these brain tissues to explore the relations between neural activity and amino acid metabolism. Differences in imaging changes will be compelling evidence.

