Based on structural data from human and animal researches, brain-imaging studies have identified a network of structures that constitute the neural circuitry for emotions, including the amygdala, cingulate, insula and prefrontal cortex. They interact to distinguish the emotional significance of stimulations, to generate and regulate affective states further.^[17,18]^ Amygdaloid nucleus is described as the “fear center” of the brain or the core of “fear network”.^[19]^ Studies have shown that PD patients have an excessive activity of the amygdaloid nucleus and Hypothalamus-Pituitary-Adrenal axis (H-P-A axis). With the improvement of the disease, the activity of amygdaloid nucleus tends to be normal. The prefrontal cortex participates in emotional processing. Anterior cingulate cortex is closely related to mood and self-control.^[20]^ As the connecting hub, insular lobe connects with the anterior cingulate cortex, amygdaloid nucleus, prefrontal cortex and other tissues which also form the circuit. Insula hyperreactivity is associated with processing negative emotional information,^[21–23]^ threat-relevant cues and symptom severity.^[24]^ Structural phase studies found abnormal volume of insula gray matter, anterior cingulate cortex and amygdaloid nucleus occur in PD patients. Functional phase studies revealed that abnormal activities of amygdaloid nucleus, anterior cingulate cortex and prefrontal cortex lead to cognitive loss and predictive anxiety,^[25,26]^ suggesting the close connection between the occurrence and development of PD and neuro-anatomic structures.

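### Sections 2.9.4 and 2.10.3 disagree on the exploratory 1H-MRS measure: Glutamate-GABA in the fear-network tissues is promised, but the only referenced quantities defined are NAA/Cr and Cho/Cr in the hypothalamus

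*Protocol article*

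**What the plan says.** Section 2.10.3 (fMRI and 1H-MRS) sets the target. Its opening sentence reads "fMRI will focus on the activity of the amygdaloid nucleus and the connection between the fear center and fear network", and the next says "1H-MRS will test the Glutamate-GABA level of these brain tissues to explore the relations between neural activity and amino acid metabolism". The Discussion identifies the region: "Amygdaloid nucleus is described as the “fear center” of the brain or the core of “fear network". It also lists "the neural circuitry for emotions, including the amygdala, cingulate, insula and prefrontal cortex". Its hypothesis is a Glutamate-GABA imbalance brought about by a fall in GABA.

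Section 2.9.4 (1H-MRS examination procedure) sets out what will be done:

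- **Site:** "1H-MRS voxels are positioned in the Hypothalamus (1.5 × 1.5 × 1.0 cm"). No other site is named.
- **Acquisition:** Point Resolved Spectroscopy at 3.0 T. No step specific to GABA is described.
- **Peaks:** NAA at 2.0 ppm and Glx at 3.8 ppm, then "GABA is located at 3.0 ppm, acetylcholine complex (Cho) is located at 3.2 ppm, creatine (Cr) is located at 3.02 ppm". The area under each is measured.
- **Derived quantities:** "The ratio of NAA, Cho to Cr is calculated with Cr as the internal standard". No other ratio is given.

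The imaging measures have their own section, apart from the primary (2.10.1) and secondary (2.10.2) endpoints, and the trial calls itself exploratory.

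**The concern.** The measure that is promised and the measure that is specified differ in region and in quantity. The GABA reading also has a technical weakness that follows from the printed peak positions.

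If 2.9.4 is followed to the letter, the referenced results are NAA/Cr and Cho/Cr in the hypothalamus. Neither metabolite in the hypothesis enters a ratio, and none of the regions named in 2.10.3 is sampled. Raw Glx and GABA areas would exist, but nothing says how to reference them or compare them between week 0 and week 12 or between groups.

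The risk lies in interpretation. Section 2.10.3 treats imaging differences as strong evidence. Hypothalamic spectra could be reported as findings about fear-network GABA, with the choice of ratio made after the data are seen.

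**Working it through.** The plan states no figure of its own to reproduce here. The check is a comparison of the two sections, followed by arithmetic on the peak positions.

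**Region**

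| Item | Source | Content |
|---|---|---|
| Tissues promised | 2.10.3 | amygdala; fear center and fear network |
| Network as listed | Discussion | amygdala, cingulate, insula, prefrontal cortex |
| Voxel site | 2.9.4 | hypothalamus |

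The stated voxel covers 0 of the 4 listed regions.

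**Quantity**

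Five peaks are located: NAA, Glx, GABA, Cho and Cr. All five areas are measured. Two ratios to Cr are formed (NAA, Cho), and 0 of the 2 involve Glx or GABA.

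**Separation from creatine**

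Inputs: positions and field strength from 2.9.4; the proton constant, 42.577 MHz/T, is a physical constant not given in the protocol.

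- Frequency at 3.0 T: 42.577 × 3.0 = 127.73 MHz.
- GABA to Cr: (3.02 − 3.00) × 127.73 = 2.55 Hz.
- Cho to Cr: (3.20 − 3.02) × 127.73 = about 23 Hz.
- Glx to Cr: (3.80 − 3.02) × 127.73 = about 100 Hz.

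**Can GABA and Cr be told apart by peak area?**

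This needs a linewidth and a GABA:Cr height ratio, which the document does not give. Assumptions: each is a single Lorentzian line, both have the same width w (full width at half maximum), and w and the height ratio are varied.

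For equal heights, two maxima appear only if w < √3 × 2.55 = 4.4 Hz. For unequal heights the limit was found numerically:

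| GABA height relative to Cr | Largest w with two maxima |
|---|---|
| 1 | 4.4 Hz |
| 1/2 | 2.7 Hz |
| 1/5 | 1.9 Hz |
| 1/10 | 1.5 Hz |

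At every width tried from 5 to 12 Hz, the two lines form one peak at all four height ratios.

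**How much creatine falls in the GABA window?**

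Take a window of ±w/2 around the GABA position, with d = 2.55 Hz. The share of the Cr area inside it is

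(1/π) × [arctan((w/2 − d)/(w/2)) + arctan((w/2 + d)/(w/2))].

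This gives 0.35 at w = 5 Hz and 0.47 at w = 12 Hz. The share of GABA's own area in the same window is (2/π) × arctan(1) = 0.50. The part of the window's signal that comes from Cr is then:

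- equal lines: 0.347/(0.347 + 0.50) = 41% at 5 Hz, and 0.471/(0.471 + 0.50) = 49% at 12 Hz;
- GABA one tenth of Cr: 0.347/(0.347 + 0.05) = 87%, and 0.471/(0.471 + 0.05) = 90%.

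**The case against.** Four points can fairly be made for the plan.

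1. **Glx and GABA areas are measured.** This stands. A reader might infer that the MRS arm cannot deliver any glutamate measure. The document does not support that: Glx has a stated position, its area is taken, and it lies about 100 Hz from Cr. What is missing is a referenced quantity built from that area.

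2. **The overlap depends on figures not in the document.** This also stands. At very narrow linewidths the two peaks would separate, so the contamination of GABA is conditional. A reader might go further and conclude that GABA/Cr would be almost constant and hide any treatment effect. No GABA/Cr ratio is planned, and without the signal ratio that conclusion is not established.

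3. **The hypothalamus is not foreign to the rationale.** The network list is introduced as non-exhaustive, and the Discussion also reports that "PD patients have an excessive activity of the amygdaloid nucleus and Hypothalamus-Pituitary-Adrenal axis". That could justify a hypothalamic voxel. It does not make the hypothalamus one of the tissues in 2.10.3, which never names it. The sections still need reconciling.

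4. **The objective is broad.** Section 2.1 speaks of relating neural activity to amino acid metabolism and names no region. To say that this objective cannot be answered would go too far: the fMRI part is untouched, and hypothalamic Glx could still be related to it.

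It could also be said that an article condenses its full protocol. That does not help here, because the article itself prints the voxel site, the peaks, the area method and the ratios, and these conflict with its own stated measure.

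**Conclusion.** The point holds as a contradiction within the plan about an exploratory mechanistic measure. Two parts rest on the text alone: the stated voxel covers none of the four listed regions, and neither of the two planned ratios contains Glx or GABA. The region conflict takes the tissues in 2.10.3 to be those named in the sentence before, which is the natural reading.

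The third part is conditional. The 2.55 Hz gap follows from the printed positions. The merging of GABA with Cr assumes Lorentzian lines of 5 to 12 Hz. On that assumption, Cr supplies from 41% of the signal in the GABA window (equal lines, 5 Hz) to 90% (GABA one tenth of Cr, 12 Hz). Glx is not affected by this overlap.

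The changes should be made, but they do not touch the primary or secondary clinical comparisons.

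**What to change.** 1. **Quantity (2.9.4).** Make Glx/Cr the planned MRS outcome, computed from the spectra already acquired, with NAA/Cr and Cho/Cr as supporting measures. Write this in before any group comparison of the spectra.
2. **Region (2.9.4 and 2.10.3).** Reconcile the two sections on voxel site. If the hypothalamus is intended, restate 2.10.3 and the conclusions as a hypothalamic measure.
3. **GABA (2.9.4, 2.10.3, Discussion).** State how GABA is separated from Cr. If it is not, do not report the area at 3.0 ppm as a GABA outcome, and remove the GABA claim.

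The work is re-analysis and rewording. No change of acquisition sequence is required; with recruitment running from December 2017 to December 2021, a change part-way could break the comparison of week 0 with week 12. Whether Glx is usable will depend on spectral quality, which the document does not describe.

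The real cost is scientific. The hypothesis is about falling GABA, so a plan resting on hypothalamic Glx/Cr supports a narrower mechanistic claim.

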### Outcome measures

2.10

#### Primary endpoint

2.10.1

The primary outcomes of this study will be changes in the frequency of panic attack and in the PDSS and PASS during the observation period (3 months) and follow-up period (1 month), analyzed in both groups. After baseline time, they will be tested at week 0, week 4, week 8 and week 12, and during the follow-up period.

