### Statistical analysis

2.14

Image data processing: using methods like independent component analysis (ICA) and function binding, applying professional software such as MRIcro for windows, Xjview 8.1, SPM 12 and MATLAB 5.1.

Statistical analysis technique: to apply a statistical test to the difference of prior-treatment and post-treatment, and to examine the curative effect difference within groups and among groups of all curative effect indexes. We will adopt the two-sided test for all statistical tests. It's considered that the tested differences are statistically significant if *P* less than or equal to 0.05. If *P* greater than or equal to .05, the tested differences are not statistically significant. Details are as following.

Measurement data: The *t* test will be adapted to run comparison among groups. When it doesn’t comply with the normal distribution, we will choose Wilcoxon rank-sum test. Similarly, we will run paired *t* test towards the difference of prior-treatment and post-treatment, and it will be changed into Wilcoxon rank-sum test while it does not comply with the normal distribution.

Enumeration data: We will use the Chi-square test, calibration Chi-square test, and Fisher exact method to run comparison among groups.

Ranked data: Wilcoxon rank-sum test will be applied to run comparison among groups and signed rank-sum test to run comparison within groups.

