## Discussion

3

PD is also known as the acute anxiety attack (AAA), one of the main patterns of manifestation of anxiety disorder.^[16]^ Repeated outbreaks of panic, tachypnea, dizziness, palpitation, tremor, and sweating are its common symptoms. Modern medicine towards perimenopausal PD has a bunch of disadvantages, for example, hormone replacement therapy could increase the risk of higher morbidity of endometrial cancer, breast cancer, and colorectal cancer. Non-hormonal medication therapy may lead to nausea and vomiting, dizziness and headache, weakness and tremor, the change of weight. More importantly, low efficiency and high relapse are the biggest problems. In recent years, therapy combining CBT with pharmacotherapy has become a hot research area of treating PD. However, it still cannot solve these problems. These existing treatments have either little effectiveness or many side effects. Because many patients are dissatisfied with current treatments, the demand for acupoint catgut embedding is increasing. ‘Keep it for a long time to cure chronic diseases’ is the theoretical guidance of acupoint catgut embedding therapy. Based on traditional acupuncture technique, this therapy is developed by using modern technology. It takes advantage of the stimulation of acupoint via physicochemical change of the suture in the human body. It is a comprehensive regulative process. However, well-designed clinical trials on the effectiveness and safety of this therapy for perimenopausal PD are not available.

This study aims at proving the clinical effect and safety of acupoint catgut embedding. Meanwhile, with the help of fMRI and 1H-MRS, investigating the pathogenesis and physio-pathology characters by revealing neural activity and amino acid metabolism of perimenopausal PD patients is a significant goal as well. There are many studies showing different mechanisms in this disease. Our laboratory runs a variety of researches aiming at the GAMA mechanism in long terms. In this mechanism, free amino acid is an iconic index. And study has also shown the changes in fMRI images of perimenopausal PD patients.

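### Three unranked primary outcomes with no deciding visit, each judged at an unadjusted P ≤ 0.05, raise the chance of a false primary result above 5%

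*Protocol article*

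**What the plan says.** Section 2.10.1 (Primary endpoint) states: "The primary outcomes of this study will be changes in the frequency of panic attack and in the PDSS and PASS during the observation period" and, in the same sentence, over the one-month follow-up. It continues: "After baseline time, they will be tested at week 0, week 4, week 8 and week 12, and during the follow-up period". No outcome is ranked first, there is no composite, and nothing says that all three must succeed. No visit or period is named as the deciding one.

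Section 2.9 (Intervention) sets the time frame: "There is a 3-months study period and a 1-month follow-up period for each group".

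Section 2.14 (Statistical analysis) applies one rule to all efficacy measures, within and between groups: "We will adopt the two-sided test for all statistical tests", and "tested differences are statistically significant if *P* less than or equal to 0.05". The methods named for measurement data are t tests or Wilcoxon tests. No joint or repeated-measures model reduces the visits to one comparison.

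Section 2.13 (Sample size calculations) uses a single two-sided α of 0.05 with 90% power, not divided among outcomes or visits, and takes its effect from the Kuppermann index, which is not one of the three primaries.

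The abstract and section 2.1 call the trial exploratory. The Discussion says: "This study aims at proving the clinical effect and safety of acupoint catgut embedding".

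**The concern.** The article fixes two things that do not fit together: several equal primary outcomes, and a significance rule that treats each test as if it stood alone. Nothing says what pattern of results makes the trial positive. A report could follow the plan to the letter and present whichever of the three outcomes, at whichever time point, reached P ≤ 0.05 as a positive primary result.

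The sample size section does not settle which outcome decides, because it rests on a different scale. Participants and treating staff are also unblinded (section 2.8), so a clear decision rule set in advance matters more than usual for outcomes such as these.

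**Working it through.** **Inputs from the article.** Three primary outcomes and four post-baseline assessments (weeks 4, 8, 12 and follow-up; week 0 is baseline) from section 2.10.1. Two-sided testing with a threshold of 0.05 from section 2.14. δ = 2.06, S = 2.12, α = 0.05, power 0.90, 20% loss and 35 per group from sections 2.13 and 2.1.

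**Input not in the article.** The correlations between outcomes and between time points. These are assumptions, shown over a range.

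**Step 1: the plan's own figure.** n = 2 × [(2.0129 + 1.3002) × 2.12 / 2.06]² = 23.25, so 24 per group and 48 in total. 48 / 0.8 = 60, and 14 × 5 = 70. The final numbers reproduce. They spend one α of 0.05 on one comparison. The article states no family-wise error rate, so there is none to reproduce.

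**Step 2: independent tests.** The chance of at least one false result among k tests is 1 − 0.95^k.
- k = 3 (three outcomes, one visit): 1 − 0.95³ = 14.3%
- k = 6 (three outcomes, two periods): 1 − 0.95⁶ = 26.5%
- k = 12 (three outcomes, four visits): 1 − 0.95¹² = 46.0%

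**Step 3: correlated tests.** Simulation of multivariate normal test statistics with no true difference: 400,000 draws, equal correlation among outcomes and equal correlation among time points. The third column counts only false results that favour embedding (nominal 2.5%).

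| Tests | Assumed correlation (outcomes / time points) | Either direction | Favouring embedding |
|---|---|---|---|
| 3 outcomes, one visit | 0 | 14.3% | 7.3% |
| | 0.5 | 12.6% | 6.3% |
| | 0.9 | 8.4% | 4.2% |
| 3 outcomes, two periods | 0.5 / 0.5 | 22% | 11% |
| | 0.5 / 0.7 | 20% | 10% |
| 3 outcomes, four visits | 0.3 / 0.3 | 42% | 22% |
| | 0.5 / 0.5 | 36% | 18% |
| | 0.5 / 0.7 | 30% | 15% |
| | 0.7 / 0.7 | 26% | 13% |
| | 0.9 / 0.9 | 15% | 7.5% |

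**Step 4: price of a correction.** For three outcomes at one visit, Holm's first threshold is 0.05 / 3 = 0.0167. With the article's δ and S and 28 per group (35 less 20%), normal-approximation power is 95.3% at 0.05 and 89.3% at 0.0167. At the full 35 per group it is 98.2% and 95.3%. These powers are only illustrative, because δ and S belong to the Kuppermann index and not to any of the three primaries.

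**The case against.** **The number of tests.** A reader might infer from section 2.10.1 that 12 between-group hypothesis tests are planned and that the false-positive rate is therefore 46%. The text does not support that as fact. The article uses the word for testing to mean measuring: section 2.9 applies it to the two imaging scans, section 2.10.3 to metabolite levels, and the sentence at issue includes week 0. That sentence is most naturally an assessment schedule. Section 2.14 speaks of differences before and after treatment and never of visit-by-visit testing. Twelve tests is thus an upper reading, and 46% also requires independence, which is unlikely for related scales measured repeatedly in the same women.

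**The direction of error.** The two-sided figures include false results that favour alprazolam. For a false claim for embedding, the absolute risk is about half.

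**The exploratory label.** It appears in the abstract and in section 2.1, whereas the stated intention to prove effect is one sentence in the Discussion. This lowers the stakes. It does not remove the problem, because the plan still designates primary outcomes, sets a yes/no significance rule and powers at 90%.

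**An unseen analysis plan.** It may specify a time point or an adjustment, and silence on those details alone would be no finding. But the article itself states three equal primaries and a 0.05 threshold for every test; an adjusting analysis plan would have to override section 2.14.

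**Conclusion.** The concern stands in a limited form. Three unranked primaries without a deciding visit, combined with an unadjusted 0.05 threshold for all tests, give a false-positive rate above the nominal level on every reading of the text. On the narrowest reading, three outcomes at one visit, it is about 8–14% in either direction (correlation 0.9 to 0). Over the two named periods it is about 20–22% at correlation 0.5 between outcomes and 0.5–0.7 between periods. The range of about 15–46% applies only if all four post-baseline visits are tested. All the ranges depend on assumed correlations.

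This should be fixed, but it does not invalidate a trial that calls itself exploratory.

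**What to change.** Before the statisticians are unblinded, amend sections 2.10.1 and 2.14 as follows:

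- Set week 12, the end of treatment, as the primary time point.
- Keep attack frequency, PDSS and PASS as the three primaries, and test the between-group differences with Holm's procedure at a family-wise two-sided 0.05: the smallest P against 0.0167, the next against 0.025, the last against 0.05, stopping at the first failure.
- Report weeks 4 and 8, follow-up and all within-group tests as supportive, with 95% confidence intervals.

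An acceptable alternative is to name one primary and test the other two in a fixed order. The article gives no reason to prefer any one of the three, and recruitment began in December 2017, so demoting two of them now could look like outcome switching. Such a change would have to be dated and justified.

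The cost is a stricter first threshold and slightly lower power (about 95% to 89% in the illustrative case above), plus an amendment. No extra patients or assessments are needed.
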